#### Box 1: A standard CDAMS/ACAS

- Case briefing between the clinician and interpreter (5mins)
- Introduction to the patient (5mins)
- Interpretation of the RUDAS (15mins)
- Ask about medical issues, mood etc. (5mins)
- Next steps (5mins)

### **5.5 Sample size justification**

The primary outcome is a score calculated using the method described above and based on that done by Ono et al [24]. A sample size of 120 (60 test and 60 control) participants (interpreters) is sufficient to detect with 80% power and alpha of 0.05, a difference in control and test group means of 1.3 with standard deviation of 2.5 (i.e. means of 2.91 control and 4.21 test in Ono et al[24]). The calculations are the customary ones based on normal distributions[33]. The target sample size is set at 150 interpreters (75 test and 75 control) to include oversampling for participant withdrawals, and because we see no foreseeable adverse effects for either group resulting from participation in the trial.

### **5.6 Statistical analysis**

To evaluate our primary outcome, we will use mixed effects generalised linear regression. Random effects will account for repeated measures from participating interpreters. Time-point (baseline, 3m and 6m) will be a categorical variable and specified as fixed. Other independent variables will be specified as fixed (intervention/control, age; sex; ethnicity; location; educational and economic attainments; and NAATI credential status).

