### *Study 2*

- 2) Interpreters trained in the MINDSET program will show an improvement in the quality of interpreted communication for dementia assessments at 3 months and 6 months following the intervention, when compared to their baseline scores.
- 3) Interpreters trained in the MINDSET program will show a greater improvement in the quality of interpreted communication for dementia assessments at 3 months and 6 months following the intervention, when compared to the control group's scores.

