### 5.2 *Randomisation*

Interpreters will be randomised into:

- a) an intervention group ( $n=75$ ) who will use the training package for 6m immediately following the randomisation, or
- b) a wait list control group ( $n=75$ ) who will receive access to the training package six months after randomisation.

This approach was chosen because it involves no deception of participating interpreters, and because both groups of interpreters will eventually have access to the training.

After enrolment in the trial, and before randomisation, participants will complete the simulated battery to measure the primary outcome of quality of interpreted communication. The test outcome will not be provided to the person until an external statistician has done the randomisation procedure (randomisation by minimisation). A researcher at National Ageing Research Institute will provide the test outcome and randomisation outcome (test/control) to the person approximately one week after doing the simulated tests. This ensures that randomisation outcome is independent of baseline scores. In this pragmatic trial, it is not possible to blind participants to group allocation when collecting the post-intervention scores. Hence, this trial is a single-blinded study where outcome assessors will be blinded to allocation.

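### Section 5.6 lists group only as a fixed effect beside time, so no term in the primary model estimates the difference in improvement at 3 and 6 months that Hypothesis 3 is about

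*Protocol*

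**What the plan says.** The analysis text for the randomised trial is Protocol Section 5.6. It names the model class, "To evaluate our primary outcome, we will use mixed effects generalised linear regression", and the random part, "Random effects will account for repeated measures from participating interpreters". The time term is "Time-point (baseline, 3m and 6m) will be a categorical variable and specified as fixed", so the baseline score is one of the three responses. Group enters through the next sentence, "Other independent variables will be specified as fixed (intervention/control, age; sex; ethnicity; location", a list that goes on to education, economic attainment and NAATI credential. Group thus stands among characteristics that do not change over time. The protocol states no product of group and time, no change score and no adjustment for the baseline score.

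The hypothesis this model has to serve is Hypothesis 3 in Section 2.2 (Study 2): trained interpreters "will show a greater improvement in the quality of interpreted communication for dementia assessments at 3 months and 6 months following the intervention", compared with control. On timing, Section 5.2 says that "before randomisation, participants will complete the simulated battery to measure the primary outcome". Section 5.5 gives 120 interpreters (60 per arm) as "sufficient to detect with 80% power and alpha of 0.05" a difference of 1.3 with SD 2.5, and sets the recruitment target at 150 (75 per arm).

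**The concern.** A greater improvement at a given visit is a difference between arms in change from baseline, which is a group-by-time contrast. A model with group and time as separate fixed effects assumes one group difference common to all three visits, including the visit before anyone was allocated. Training cannot have acted at that visit, yet it carries a third of the weight in the group coefficient.

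Two things are at stake if the model is run as listed. The reported effect would be too small by a known fraction, and there would be no separate result at 3 or 6 months. The sample size in Section 5.5 was computed for the full difference between two group means, so the power stated there would not describe the analysis in Section 5.6.

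**Working it through.** **Inputs from the protocol.** Difference 1.3, SD 2.5, 60 per arm, 80% power and alpha 0.05 (Section 5.5); three visits with baseline before randomisation (Sections 5 and 5.2).

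**Assumptions.** The protocol gives no within-person correlation r, so a range is shown. Variances are equal, the correlation is the same between any two visits, data are complete, the test is two-sided with a normal approximation, and the listed covariates explain nothing.

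**1. The protocol's own figure.** n per arm = 2 × (1.960 + 0.842)² × 2.5² / 1.3² = 58.05, rounded up to 59. At 60 per arm, SE = 2.5 × √(2/60) = 0.456, and power = Φ(1.3/0.456 − 1.96) = 0.81. The stated 60 per arm reproduces.

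**2. What the group coefficient estimates.** In the balanced model it is the mean of the three visit-specific group differences. With a true effect of 1.3 at both follow-up visits:

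(0 + 1.3 + 1.3) / 3 = 0.867, two thirds of the effect.

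With an effect of 1.3 at 3 months only, it is 1.3/3 = 0.43. In 150 simulated trials at r = 0.5, fitted with a random-intercept model, the group coefficient averaged 0.845. In the same trials the group-by-3-month term averaged 1.294.

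The coefficient is also not a measure of improvement. Suppose the arms differ by 0.5 at baseline and stay 0.5 apart: the coefficient is 0.50 with no difference in improvement. Suppose the trained arm starts 1.0 lower and ends 0.5 higher: it has improved by 1.5 more, and the coefficient is (−1.0 + 0.5 + 0.5)/3 = 0.

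**3. Type I error.** With no group difference at any visit, 4,000 simulated trials at each of r = 0.3, 0.5 and 0.7 rejected in 4.7% to 5.1% of runs.

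**4. Power at 60 per arm, true effect 1.3 at both follow-up visits.** Standard errors:

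- As listed: 2.5 × √[2(1 + 2r)/(3 × 60)], against an expected estimate of 0.867.
- Group-by-time, unadjusted change at one visit: 2.5 × √[4(1 − r)/60], against 1.3.
- Baseline-adjusted contrast at one visit (common baseline mean or baseline covariate): 2.5 × √[2(1 − r²)/60], against 1.3.

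| r | 0.1 | 0.2 | 0.3 | 0.5 | 0.7 |
|---|---|---|---|---|---|
| SE as listed | 0.289 | 0.312 | 0.333 | 0.373 | 0.408 |
| Power as listed | 85.1% | 79.4% | 73.9% | 64.3% | 56.5% |
| Power, unadjusted change | 56.5% | 61.5% | 67.3% | 81.3% | 95.7% |
| Power, baseline-adjusted | 81.7% | 82.8% | 84.7% | 90.8% | 97.9% |

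Example at r = 0.5, as listed: Φ(0.867/0.373 − 1.96) = Φ(0.37) = 0.64. Setting power to 80% and solving gives r = 0.19.

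**5. If all 75 per arm are retained.** Power as listed is 82.8% at r = 0.3, 73.9% at r = 0.5 and 66.0% at r = 0.7. The baseline-adjusted contrast has 91.6%, 95.7% and 99.4%.

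**The case against.** Section 5.6 is a few sentences that sort variables into random and fixed. It gives no equation, does not say that only main effects will be fitted, and does not say which coefficient tests Hypothesis 3. The interaction is left out, not ruled out. The intended comparison is clear from Section 2.2 and from the lay summary in Section 1.1, and an analysis plan that is not at hand may state the contrast. This stands as a limit on the finding: the documents do not show that the sponsor means to rely on a main effect. It does not remove the finding, because the protocol goes beyond silence. It lists the fixed terms of the primary model, and that list does not contain the term its hypothesis needs.

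Three stronger readings are tempting, and the documents do not support them.

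- **That the model is unable to test for a training effect, or that its test is invalid.** Because allocation is randomised, the coefficient has expectation zero when training has no effect at any visit, and its error rate stays near 5%. The bias is towards zero.
- **That power must fall below 80%.** This depends on a correlation the protocol does not give. At 60 per arm, power is 85.1% at r = 0.1 and 79.4% at r = 0.2. With 75 per arm retained it is 82.8% at r = 0.3.
- **That adding the interaction is enough to recover power.** At r = 0.3 an unadjusted change contrast has 67.3%, less than the 73.9% of the model as listed. At low correlation, the gain comes from using the baseline score.

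**Conclusion.** The point holds. The listed model has no parameter for the difference in improvement at 3 or 6 months, and its group coefficient is two thirds of a constant effect (0.87 for a true 1.3). That attenuation follows from giving equal weight to three visits, one of them before randomisation, and does not depend on the correlation. The loss of power does depend on it: at 60 per arm, power is under 80% from r of about 0.2 upward and reaches 56.5% at r = 0.7. These figures assume the same effect at both follow-up visits, complete data and no gain from the listed covariates. The sample size of 120 reproduces and is not in question.

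**What to change.** In Section 5.6, keep the baseline, 3-month and 6-month scores as responses, replace the group main effect with group-by-time terms at 3 and 6 months, and constrain the two arms to a common baseline mean. A close alternative is to model the 3- and 6-month scores with the baseline score as covariate, plus group, visit and group-by-visit. The two are not identical when baseline or follow-up scores are missing, so the text should choose one. Either way, name the group contrasts at 3 and 6 months as the test of Hypothesis 3. The baseline constraint or covariate should be part of the change, for the reason shown by the 67.3% figure above. The cost is a short amendment to Section 5.6, carried into the analysis plan. It needs no new data and no change to the sample size.

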## 6 Study 3 – Implementation of training

In Study 3, we will follow World Health Organization guidance for scaling up health service innovations [34] to implement the training among eligible Victorian interpreters. By doing so, we will monitor, evaluate, and adapt the training to real-world circumstance, and then use the lessons learned to guide our national and inter-state partners for Australia-wide implementation.

Following study 2, the training will be rolled out to all NAATI certified interpreters across Victoria. We will conduct two rounds of qualitative semi-structured interviews: first with interpreters and managers while implementation is underway and second with clinicians once implementation is complete.

### 6.1 *Promotion of the training to interpreters*

There are currently 1,613 NAATI interpreters in the nominated languages based in Victoria. To reach them and encourage them to take up the training, we will use multiple channels to tell a compelling story and build coalitions and networks to promote the training [34]. Eligible interpreters will be identified and formally invited by NAATI to complete the MINDSET training. Promotional messages about the MINDSET training will also be circulated by AUSIT, All Graduates, and Dementia Australia. Interpreter testimonies will be used to build motivation and emails will be sent to the CEOs/relevant heads of interpreter agencies (e.g. Translating and Interpreting Services (TIS National), Language Loop, Polaron, On Call), with whom we have established relationships, to inform them about the free training, and ask them to encourage their eligible interpreters to participate.

These strategies will be repeated at different points during the implementation period. All interpreters who complete the training will receive CPD points.

### 6.2 *Monitoring*

We will monitor implementation in Victoria through data collected as part of NAATI's online training platform, where the training modules are hosted. The following data will be collected:

- a) Baseline covariates of interpreters taking up the training (age, sex, ethnicity, location, educational and economic attainments, and NAATI credential status)
- b) Total uptake (number of completions),
- c) Rate of uptake (completions/per week),
- d) Geographic coverage (via postcode).

The training will be considered implemented when 70% of eligible Victorian interpreters (n=1,129) have completed the training. The monitoring will help us identify any barriers to implementation and to assess whether economies of scale are being reached (i.e. 70% coverage across metro and regional areas).

### 6.3 *Evaluation*

To understand the process of implementation, once we reach 50% of our target (i.e. 35% coverage) we will begin telephone/video interviewing 20-30 interpreters and interpreter agency managers to understand: training uptake, potential facilitators/barriers and solutions; and whether the essential features of the training are being adhered to in practice (and if not, what remedial action can or should be taken). This will allow us to make necessary adjustments.

Once we reach 70% of our target (i.e. 50% coverage), ~20 clinicians from high CALD caseload CDAMS will be interviewed to understand if the training improved interpreter communication, impacted practice, and clinician satisfaction.

### **6.3.1 Participant eligibility**

#### *Interpreters*

Eligible interpreters who have completed the training will be identified by NAATI and invited to participate in interviews. To be eligible for interviews, interpreters must:

- a) Be NAATI credentialed with provisional certification or professional certification;
- b) Have 6+ months practicing experience;
- c) Have access to an internet connection;
- d) Interpret for Greek, Italian, Mandarin, Cantonese, Arabic or Vietnamese languages;
- e) Reside in Victoria; and
- f) Have not participated in studies 1 or 2.

Interpreters will be remunerated by our industry partners according to a standard hourly interpreting rate for time spent participating in interviews.

#### *Managers*

The research team will contact eligible managers from key interpreting agencies to take part in interviews. To be eligible managers must be working in a leadership role at an interpreting agency in Victoria with oversight of interpreter CPD.

#### *Clinicians*

There are 21 Cognitive Dementia & Memory Service (CDAMS) clinics in Victoria (11 Melbourne/10 regional). We will obtain names and contact details of high CALD caseload CDAMS from All Graduates. High caseload clinics will be sent an email describing the study and inviting their clinicians to participate in an interview. Non-responders will get a reminder letter and phone call.

## 633 7 Participant Safety and Withdrawal

### 634 7.1 *Consent*

635 The research staff who contact people living with dementia during study 1 will be trained to  
636 recognise signs that the person does not fully understand the implications of participating in  
637 research. For example, the potential participant may think they are receiving a service from  
638 NARI or they may not be able to sufficiently orient themselves to time and place to be able to  
639 schedule an appointment for the interview. When conducting qualitative interviews, the  
640 researcher will again assess the potential participant's capacity to give consent.

641 Capacity to provide consent will be determined by whether the potential participant:

- 642 • Understands the nature of the research and their participation in the research;
- 643 • Appreciates the consequence of their participation;
- 644 • Shows the ability to consider alternatives including the option to not participate;
- 645 • Shows the ability to make a reasoned choice.

646 Written and verbal techniques will be used to communicate the details of the research, and  
647 the potential participant will be asked to explain the details back to the researcher. This  
648 approach is recommended by the Dementia Collaborative Research Centres as cognitive  
649 decline can be specific to one or more cognitive processes and a general cognitive screen may  
650 not be the best way to judge a person's capacity to give consent to participate in research.

651 Researchers will follow the 'Decision Tree for Respecting Dissent and Seeking Assent for  
652 Dementia Research' [35] (See Figure 2) throughout recruitment and interviews with  
653 participants living with dementia. If the researcher thinks that capacity is impaired and  
654 informed consent is not valid, then the potential participant will be politely dissuaded from  
655 participating in the study and offered instead to be put on the NARI mailing list to receive a  
656 quarterly newsletter. This approach is considered less invasive than conducting a formal  
657 cognitive test with someone who may not have capacity to consent to the test or involving the  
658 potential participant's medical practitioner.

[figure not shown]

Figure 2. Decision Tree for Respecting Dissent and Seeking Assent for Dementia Research.  
Source: Black et al. 2010 [35]

## 7.2 Risk management and safety

There are no obvious disadvantages or risks associated with the participation of subjects in this study. However, participants with cognitive impairment may have increased susceptibility to some forms of discomfort or distress. The research team have experience in working with people with cognitive impairment on previous research projects. Every effort will be taken to ensure these risks are mitigated as much as is possible. The research staff will be observant to the impact of information on the potential participant during interviews, providing appropriate rests, involving people familiar to the potential participant and ceasing any subjectively distressing interaction in a timely manner.

The potential risks will be reduced by the research team stressing that participation is strictly voluntary, and the participant can withdraw at any time without negative repercussions. The informed consent process will also highlight the nature of the study and the types of questions that will be asked.

If by taking part in this project, the participants suffer any injuries (including but not limited to physical or psychological distress) or complications as a result of this research project, the participants will be encouraged to contact the study team as soon as possible and they will be assisted with arranging appropriate treatment. If they are eligible for Medicare, they can receive any medical treatment required to treat the injury or complication, free of charge, as a public patient in any Australian public hospital. Any counselling or support will be provided by qualified staff who are not members of the research project team. This counselling will also be provided free of charge.

Participants may have existing relationships with their service provider organisations that have agreed to be study partners. For example, people with dementia may be recipients of interpreter services or dementia-related medical care, interpreters will be credentialed by the National Accreditation Authority for Translators & Interpreters (NAATI), and clinicians may have utilized interpreting services. The research team will be present for and monitor all contact between participants. Whether clients, family carers, clinicians, or interpreters take part in this research project, or not, should not have any bearing on their future relationship with their service provider, their employer, or accreditation body.

For interpreters, they will be assured that their consent is not coerced, that their participation is entirely voluntary and will not affect their relationship with their employer (Interpreter service) or the accreditation body (NAATI). Interpreters will be required to give informed consent before participating in the study and will be informed (both verbally and in writing) that they are free to withdraw from the study at any time.

For the co-design workshops, it is also possible that clinicians may be participants with interpreters they have worked with in the past. However, the research team are aware of the potential for unequal relationships and will not place familiar participants in the same co-design groups.

### **7.3 *Handling of withdrawals***

For participants who wish to withdraw after data has been collected, the data collected up to that time will form part of the research project results. Participants will be informed of this at the time of consent, on their PICFs.

#### **7.3.1 People with dementia**

Participants may withdraw from the interviews at any time. If they consent to participate but change their mind and do not wish to continue their involvement, the decision will be respected, and a replacement sought. People with dementia are not part of study 2 or 3.

#### **7.3.2 Family carers**

Participants may withdraw from the workshops at any time. If they consent to participate but change their mind and do not wish to continue their involvement, the decision will be respected, and a replacement sought. Carers are not part of study 2 or 3.

### 713 **7.3.3 Interpreters**

714 Participants are free with withdraw at any time from any of the three studies, with no effect  
715 on their relationships with the researchers, NAATI, or their employers. If they consent but  
716 then change their mind, the decision will be respected, and a replacement sought.

### 717 **7.3.4 Clinicians**

718 Participants are free with withdraw at any time from Study 1 and 3, with no effect on their  
719 relationships with the researchers or their employers. If they consent but then change their  
720 mind, the decision will be respected, and a replacement sought. Clinicians are not part of  
721 Study 2.

## 722 **7.4 *Replacements***

### 723 **7.4.1 Study 1**

724 If there is time to organize a replacement, then the withdrawn participant will be replaced. If  
725 workshop participants withdraw on the day of the workshop, then no replacement will be  
726 made.

### 727 **7.4.2 Study 2**

728 If there is time to organise a replacement then the withdrawn participant will be replaced, up  
729 until the end of the first data collection point (baseline). As our study design requires 120  
730 (60/60) participants to power study, our target of 150 (75/75) allows for some drop-out.  
731 However, if we anticipate that the target of 120 will not be reached, we may continue  
732 recruiting participants after the end of the first data collection point.

